#### The risk estimation and lifestyle assessment

The risk estimation is based on the widely accepted FINDRISK score and is specified for predicting CMD in the Dutch population [25,26]. This seven item-questionnaire can be completed by self-report and assesses cardiometabolic risk factors including age, gender, body mass index, waist circumference, current family history of cardiovascular disease and/or diabetes [13,26]. The lifestyle assessment consists of questions involving smoking, physical activity, dietary patterns and willingness to change lifestyle [9,12].

The threshold in the risk estimation that will be used is an absolute risk for developing CMD in the next seven years of ≥ 23% for men and ≥ 19% for women [26]. Patients with scores below the threshold are at low risk and receive online tailored lifestyle advice based on the reported risk factors and the information provided in the lifestyle assessment. All patients with scores above the threshold are advised to complete their final risk profile with additional measurements, by making an appointment at their general practice.

#### Completing the CMD risk profile

At the general practice, the risk profile is completed by additional measurements: serum cholesterol level, fasting glucose level and blood pressure. During a second visit the final risk profile is calculated based on the SCORE risk estimation [27].

#### Treatment of patients with an increased risk for CMD

Patients will receive treatment according to their risk profile, based on recommendations on lifestyle advice and drug treatment from guidelines issued by the Dutch College of GPs (including guidelines on cardiovascular risk management, obesity management and diabetes mellitus). Participating practices offer lifestyle interventions in their own conventional manner, with the facilities available to them. Possible facilities for lifestyle interventions include the aid of a lifestyle coach to support active lifestyle change, offering structured programs for smoking cession services, weight management or exercise programs and collaboration with other local initiatives in health programs.

### Control group

Patients allocated to the waiting list control group receive an invitation from their GP - at the same moment the first intervention group is invited- to participate in a health study by completing an online questionnaire including the questions of the risk estimation and lifestyle assessment. However, these patients neither receive a risk score, nor a specific lifestyle advice. These patients will start with a one year waiting period, to be used as control comparison. After a year they are invited to participate in PPA CMR, starting with completing the risk estimation and lifestyle assessment online. Hence, the waiting list control group is offered the identical route as the intervention group. Patients in the waiting list control group receive normal standardized care during the waiting period, including lifestyle advice or diagnostics and treatment for CMD when indicated.

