## Methods

### Study design

The INTEGRATE study is a clustered stepped-wedge randomized controlled trial with a waiting list control group. A flowchart of the study and a timeline is shown in Figures 1 and 2, respectively. All participants are offered the intervention (PPA CMR) during the study period. The intervention is implemented over four time periods, in randomly ordered subgroups. The intervention group starts with PPA CMR at onset of the study, the control group starts with PPA CMR one year later. The one year waiting list period is necessary to measure natural changes in lifestyle and to estimate the number of patients with newly detected CMD without exposure to PPA CMR.

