### Randomization

Eligible patients are randomized within each general practice into four time groups: two intervention groups and two waiting list control groups. We will use the statistical software program Stata version 12 for the randomization. Every four months a new group starts with the intervention, starting with the two intervention groups. After twelve months the two waiting list control groups will sequentially start with PPA CMR.

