#### Waiting list control group

From the waiting list control group we establish risk profiles, lifestyle assessment, health status, work status and absence from work at baseline and again at the start of PPA CMR one year later. At the start of PPA CMR newly detected patients with CMD will be established, based on ICPC-1-coded diagnoses in the EMRs. Patients who develop a new CMD - documented through an ICPC-1-coded diagnoses in the EMR - will not be eligible for participation in PPA CMR, but will receive questionnaires for follow-up. When the waiting list control group starts with the intervention phase, the patients follow the identical route as the intervention group (see Figure 2).

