### Implementation challenges

Due to health care policy there is a possibility that changes in the health care environment will occur over time. For example, changes in established compensations for participation in prevention programs by health care insurers can influence the compliance and participation rates. However, these changes will occur in both the intervention groups and the waiting list control groups equally, so we expect this will not influence our study results.

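### The baseline, waiting and follow-up rules contradict each other for the second waiting-list group; followed as written, its one-year control period runs to about 16 months

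*Protocol article*

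**What the plan says.** Randomization: patients are "randomized within each general practice into four time groups: two intervention groups and two waiting list control groups". On timing, "Every four months a new group starts with the intervention, starting with the two intervention groups", and "After twelve months the two waiting list control groups will sequentially start with PPA CMR". No month is given for the second waiting-list group.

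Control group: waiting-list patients, with no split between the two groups, are sent their questionnaire "at the same moment the first intervention group is invited". The section continues: "These patients will start with a one year waiting period, to be used as control comparison".

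Study design treats the waiting list as one block: "the control group starts with PPA CMR one year later".

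Waiting list control group (under Endpoints and measurements): questionnaires are repeated when PPA CMR begins, said to be a year after baseline. For diagnoses: "At the start of PPA CMR newly detected patients with CMD will be established, based on ICPC-1-coded diagnoses in the EMRs".

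Table 2 defines the first primary endpoint over one year of follow-up. Intervention patients are measured at their own start of PPA CMR and twelve months later.

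Implementation challenges, on changes in the health care environment: "these changes will occur in both the intervention groups and the waiting list control groups equally".

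**The concern.** For the second waiting-list group the text sets four conditions: a month-0 baseline, a start after the first waiting-list group, outcomes taken at that start, and a wait of one year. At least one must give way. If the stated mailing and measurement rules are followed, the period described as a year is the one that gives way.

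Two primary endpoints depend on it. Newly detected CMD could be counted over a longer period in part of the control arm, which would understate the extra detection by PPA CMR. Change in risk factors, which includes the smoking outcome behind the sample size, would compare a 12-month change with a longer one that also ends at a different time of year from where it began. The modelled long-term outcomes and the cost-effectiveness analysis take one-year changes and the waiting-list comparison as inputs, so they would carry the error forward. A larger sample does not remove it.

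**Working it through.** **Inputs.** Four groups, two per arm, and a four-month step between starts (Randomization). Waiting-list baseline at month 0 (Control group). Control outcomes at the start of PPA CMR (Waiting list control group). Intervention follow-up of 12 months from each group's own start (Endpoints and measurements). Assumed: the four-month step also separates the two waiting-list groups.

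**Windows.** Length = follow-up month − baseline month.

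| Group | Baseline | Follow-up | Length |
|---|---|---|---|
| Intervention 1 | 0 | 12 | 12 |
| Intervention 2 | 4 | 16 | 12 |
| Waiting list 1 | 0 | 12 | 12 |
| Waiting list 2 | 0 | 12 + 4 = 16 | 16 |

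The plan's own figure of one year is reproduced for the first waiting-list group, whose window coincides with that of the first intervention group. It is not reproduced for the second: 16 / 12 = 1.33, a third longer. If the gap between the waiting-list starts is d months rather than four, the window is 12 + d, so the conflict exists for any d above zero.

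**Alternative readings of the second waiting-list group.**
- Outcomes at month 12, start of PPA CMR later: lengths agree, but this contradicts the rule that outcomes are taken at the start of PPA CMR. All controls then cover months 0–12, which overlaps the second intervention group's 4–16 for 8 of 12 months.
- Both waiting-list groups start at month 12: contradicts the sequential start.
- Baseline at month 4: lengths agree and both waves match, but this contradicts the single baseline in the Control group section.

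**Effect on the count of new CMD if codes up to the start of PPA CMR are included.** The documents give no rate, so a range is assumed. With constant annual rate r, the cumulative proportion at t months is F(t) = 1 − exp(−r·t/12). With equal waiting-list groups (assumed), the pooled ratio is [F(12) + F(16)] / [2·F(12)].

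| r per year | F(12) | F(16) | F(16)/F(12) | Pooled ratio |
|---|---|---|---|---|
| 1% | 0.00995 | 0.01324 | 1.331 | 1.166 |
| 3% | 0.02955 | 0.03921 | 1.327 | 1.163 |
| 5% | 0.04877 | 0.06449 | 1.322 | 1.161 |
| 10% | 0.09516 | 0.12483 | 1.312 | 1.156 |

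The excess is therefore about 16 to 17%. With a share w of controls in the second group, the ratio is 1 + w × (0.312 to 0.331): 1.10 to 1.11 at w = 1/3, and 1.21 to 1.22 at w = 2/3.

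**If codes are cut at month 12**, F(12) applies to both waiting-list groups and the ratio is 1.00. Questionnaire changes in the second group still run from month 0 to about month 16.

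The sample size of 721 does not depend on any of this.

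**The case against.** The strongest reply is that no sentence says any control patient is followed for 16 months. The text states one year repeatedly, month 16 is an inference, and the timeline in Figure 2, which was not available for this review, may give separate baselines for the two groups. That stands against treating 16 months as established. It does not remove the conflict: whatever the figure shows, the Control group wording gives one baseline for all waiting-list patients, and at least one sentence must change.

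Second, Table 2 limits the first endpoint to one year, so codes after month 12 arguably never count. This also stands, and it makes the 16 to 17% conditional. It does not help the questionnaires, for which no separate month-12 mailing to the second waiting-list group is described.

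Third, all patients are selected and randomized at baseline (Discussion, Choices in study design). If new codes were counted from selection, the second intervention group would also accrue about 16 months by its follow-up, and the arms would balance on average at (12 + 16) / 2 = 14 months. That is possible for the coded diagnoses, but it departs from the one-year definition and leaves the questionnaire windows as they are.

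Fourth, the windows overlap heavily. Months 0–16 contain both intervention windows, and randomization within practice means that both arms share the same practice environment. A reader might infer that the control arm is not concurrent, or that the statement about equal exposure to external change is false. Neither is supported: the first waves match exactly, and the statement is only not fully secured for the second.

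**Conclusion.** The contradiction is real and affects one of the two waiting-list groups. Applied as written, the baseline and follow-up rules give that group a window of about 16 months against 12 in the intervention groups, provided that the four-month step applies to it. No control window then matches the second intervention group's months 4–16.

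The size for newly detected CMD is conditional. The pooled control proportion is about 16 to 17% too high if codes are counted to the start of PPA CMR, the waiting-list groups are equal in size and the rate is constant between 1% and 10% a year. It is zero if counting stops at 12 months. For the risk-factor endpoint, the unequal period remains under the stated rule whichever way codes are counted; the documents give no figure from which to size a seasonal or time effect.

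A reader might go further and say that a true detection ratio of 1.50 would appear as 1.50 / 1.167 = 1.29. The 1.50 is not in the documents, and the result also needs codes after month 12 to count, so it should not be presented as the expected bias.

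The point goes beyond analysis-plan detail because it concerns when questionnaires are sent. Coded diagnoses can be cut to a common window afterwards. A baseline questionnaire sent at the wrong time cannot be recreated.

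**What to change.** 1. State the baseline and follow-up months for each of the four groups, and bring Study design, Randomization, Control group and Waiting list control group into line with them.
2. Send the second waiting-list group its baseline questionnaire together with the second intervention group (month 4). Take its outcome 12 months later, just before it enters PPA CMR. The waves then have matching windows in both arms: 0–12 and 4–16.
3. Count coded CMD in the EMR over a fixed 12 months from each wave's baseline, in both arms.
4. Compare within wave, with wave as a stratum in the multilevel models. The statement in Implementation challenges about equal exposure then rests on matched windows.

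The cost is one mailing moved by four months and one model term. The EMR count needs only a common cut-off rule.

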#### Response-enhancing strategies

During this study we will develop and evaluate different response-enhancing strategies in subgroups of the waiting list group. The response enhancing strategies are adjusted according to the results of non-response analyses performed early in the study (see next paragraph, endpoint 5). Possible strategies include reminders by telephone, translated questionnaires for non-Dutch speaking patients, information gatherings at the general practice and verbal reminders by the GP.

Another strategy is using a toolbox to complete the final risk profile at home. It offers the option to bypass one or both of the GP consultations. The toolbox contains a blood pressure device and a laboratory test form. Patients are asked to measure their blood pressure, visit the laboratory and to complete the results online. In case of a high blood pressure and/or elevated serum cholesterol or glucose levels, patients are advised to consult their GP. Patients without elevated biomedical risk factors receive an online tailored lifestyle advice and will therefore bypass both GP consultations. Like the other response-enhancing strategies, the toolbox option will be implemented during the intervention period of the waiting list control group.

### Endpoints and measurements

The endpoints of the INTEGRATE study are shown in Table 2. An overview of all measurements is shown in Figure 2.

**Table 2 T2:** Primary and secondary endpoints

**Primary endpoints**	**Secondary endpoints**
1. The number of newly detected patients with a CMD in one year follow-up	1. Difference in primary outcome 5 after implementation of different response-enhancing strategies
2. Change in individual risk factors (smoking, physical inactivity, obesity, unhealthy diet, blood pressure and cholesterol levels) for CMD between baseline and one year follow-up	2. Change in willingness to change lifestyle between baseline and one year follow-up
3. The expected number of newly detected patients with CMD and mortality after 5, 10,20 years and lifetime	3. Change in health status between baseline and one year follow up
4. Costs-effectiveness of PPA CMR	
5. Non-participation and compliance in different stages of PPA CMR	

For our secondary endpoints we will use the information provided for our primary endpoints.

1. *Newly detected patients with CMD at baseline and one year follow-up*

The number of newly detected patients with pre-existing CMD will be established after the second consultation and after one year follow-up, based on ICPC-1-coded diagnoses (see Table 1) in the EMRs.

2. *Change in individual risk factors for CMD between baseline and one year follow-up*

For patients with an increased risk for CMD, risk and lifestyle profiles will be established at the start of PPA CMR and after twelve months of follow-up. Risk profiles consist of the completed risk profile including the additional measurements done by the GP or with the self-management toolbox. The questions of the online risk estimation and lifestyle assessment are repeated after six months as well (see Figure 2).

For patients with a low risk for CMD we will establish risk and lifestyle profiles at the start of PPA CMR and after twelve months of follow-up. These risk profiles do not contain the additional measurements.

3. *Expected newly detected patients with CMD and mortality after 5, 10, 20 years and lifetime*

We will use the RIVM-Chronic Disease Model (RIVM-CDM) [28,29] to extrapolate the number of possible prevented CMD due to PPA CMR with a time horizon of 5, 10 and 20 years. The calculations are based on changes in risk profile during one year of treatment.

4. *Costs-effectiveness of PPA CMR*

For patients with an increased risk for CMD, we will establish health status, work status and absence from work at the start of PPA CMR and after six and twelve months of follow-up. Health status is measured by the validated Dutch version of the SF-36 [30] and the EQ-5D [31,32]. Work status and absence from work is measured by using parts of the Productivity Cost Questionnaire (iPCQ) [33].

Healthcare and non-healthcare costs are measured after six and twelve months of follow-up. Healthcare costs include the costs of implementing PPA CMR and any lifestyle intervention or treatment that emanates from the use of PPA CMR. Other healthcare costs are the costs of health care utilization during the one year follow-up. These costs are based on standard prices for health care use [34]. Non-healthcare costs include expenses made by participants during the study, e.g. own expenses for lifestyle interventions. Data on health care use, needed for the economic evaluation, will be extracted from EMR’s of GPs.

For patients with a low risk of CMD we will establish health status, work status and absence from work at the start of PPA CMR and after twelve months of follow-up.

After completion of PPA CMR, the willingness to pay for (parts of) this program is evaluated in all participants.

5. *Non-participation and compliance in different stages of PPA CMR*

Participation rates in the different phases of PPA CMR are measured by establishing the number of participants and the number of eligible patients in each stage (after the first invitation, after completion of the online risk estimation, after completing the risk profile and during the treatment phase). Data about the numbers of participants in each phase can be derived from the website for online respondents. The number of practice visits and compliance with treatment is established at six and twelve month with data from EMRs and self-reported compliance. We will collect information on determinants of response and non-response through the use of three different sources. First, we will send questionnaires to a random sample of patients who did not respond to the invitation of their GP for participating in PPA CMR (non-response group 1). This non-response questionnaire contains items on health risk behavior, assumptions about CMD and screening, reasons for not participating and attitudes towards response-enhancing strategies (see Table 3). In addition, we will send a comparable online non-response questionnaire to patients who scored above the threshold on the online risk estimation, but did not consult their GP (non-response group 2). Second, we will extract anonymized data from EMRs, including information on health care utilization of both participants and non-participants. Finally, all data will be linked with data from Statistics Netherlands to obtain information about socio-economic status (SES) and ethnic background.

**Table 3 T3:** Overview of measurements among non-responders

**Non-response questionnaire**	**T=0**	**T=12**
Risk estimation (paper)	*	
Online risk estimation and lifestyle profile	o	o
Attitude towards screening and treatment of CMD	•	
Reasons for non-participation	•	
Attitude towards response-enhancing strategies	•	
Newly detected CMD (EMR)		•
Health care utilization (EMR)		•

* = Non-responders group 1 (no response to invitation PPA CMR, no online risk estimation).

o = Non-responders group 2 (score above threshold on risk estimation, but not no GP consultation).

• = All non-responders (group 1 + 2).

Information on determinants of non-participation and successful completion of PPA CMR is used to study the differences in characteristics of responders and non-responders. We will also study differences in characteristics of participating practices (e.g. urban/rural locations, solo/group practices, organization of lifestyle interventions) to find practice-related factors that are associated with participation and compliance rates. The analyses of determinants for participation shall be performed in the first groups starting with the intervention. Depending on the findings, response-enhancing strategies are developed and implemented in the waiting list control groups that subsequently enter the study. Data collection for subgroups receiving a response enhancing intervention is done in the same way as described above.

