#### Cost-effectiveness of PPA CMR

We will perform an economic evaluation to relate net incremental costs and effects of PPA CMR compared to the waiting list control group. Estimated costs are based on the healthcare and non-healthcare costs. After one year of follow-up, cost-effectiveness of PPA CMR will be established. To evaluate cost-effectiveness in the long term, modeling is required. We will use the RIVM-Chronic Disease Model (RIVM-CDM) to perform this long-term economic evaluation. The RIVM-CDM is a Markov-type, dynamic population-based model [28,29] and is able to relate changes in prevalence of risk factors to changes in future incidence of CMD. The model also contains data on costs of cardiovascular events and associated losses in quality of life. This model has extensively been used for the evaluation of cost-effectiveness of prevention programs targeted at lifestyle improvement [34,36-38].

The cost-effectiveness will be calculated per level of change in individual risk factors. Incremental cost-effectiveness ratios (ICER) are derived from calculating the net costs of PPA CMR compared to the waiting list control group, divided by its effect. In addition, we will calculate the incremental cost-utility ratios (ICUR). Therefore, the incremental costs of PPA CMR compared to the waiting list control group will be divided by the effects in quality adjusted life years (QALY’s) gained. Utility values as incorporated in the RIVM-CDM will be used for future cardiovascular events. Probabilistic sensitivity analysis are performed for all calculations.

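### Primary endpoint 3 counts CMD and deaths over a lifetime: all-cause deaths in a cohort followed for life cannot differ between arms, and the CMD count is ambiguous in direction

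*Protocol article*

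**What the plan says.** In the protocol article, section Endpoints and measurements, the primary column of Table 2 has as its third entry "The expected number of newly detected patients with CMD and mortality after 5, 10,20 years and lifetime". The heading of item 3 below the table repeats it: "Expected newly detected patients with CMD and mortality after 5, 10, 20 years and lifetime". The lifetime horizon is therefore not a slip in the table.

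The method text under that heading is narrower. The RIVM-CDM will be used "to extrapolate the number of possible prevented CMD due to PPA CMR with a time horizon of 5, 10 and 20 years", and "The calculations are based on changes in risk profile during one year of treatment". It mentions neither a lifetime horizon nor mortality. Nowhere does the article say whether mortality is all-cause or CMD-specific.

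The section Cost-effectiveness of PPA CMR describes the model: "The RIVM-CDM is a Markov-type, dynamic population-based model", which "is able to relate changes in prevalence of risk factors to changes in future incidence of CMD". For the cost-utility ratio, incremental costs "will be divided by the effects in quality adjusted life years (QALY’s) gained". QALYs are thus planned, but under endpoint 4 and not endpoint 3.

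**The concern.** A count of events by a fixed time can show that a programme delays or prevents them. Over a whole lifetime this breaks down for deaths, because delay is the only possible benefit and the count ignores delay. For CMD the count mixes two effects that pull in opposite directions: fewer new cases per year at risk, and more years at risk.

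The Discussion gives reduction of cardiometabolic morbidity and mortality as the final goal, and item 5 of the design choices (Modeling) says that the model is needed because benefit appears only in the longer term. At its longest horizon, a primary endpoint could then report no effect on mortality, and possibly more CMD, for a programme that lengthens life. Adding the word lifetime to the method sentence would make the text consistent but would leave this problem in place.

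**Working it through.** The plan states no figure for endpoint 3, so there is none to reproduce. Only the smoking effect, 25% against 20%, comes from the documents (Sample size calculation). All rates below are assumptions for illustration.

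**1. Lifetime deaths (no rates needed).** Let S(t) be the proportion alive at time t in a closed cohort of N people. Deaths by time T are N × [1 - S(T)], so the arms differ by N × [S_control(T) - S_intervention(T)]. At the end of life both S are 0 and the difference is 0. Life-years gained are N × ∫[S_intervention(t) - S_control(t)] dt, which is positive whenever survival improves.

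**2. Lifetime CMD.** The count is N × ∫ A(t) × h(t) dt, where A(t) is the proportion alive without CMD and h(t) the CMD hazard. A programme that lowers h(t) and mortality also raises A(t). The sign depends on which effect is larger.

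**3. Illustration with the planned smoking effect.** Three states (no CMD, CMD, dead), from age 57 to 120, t in years. CMD hazard is 0.01 × 2^(t/12). Death hazard is 0.0045 × 2^(t/8), doubled after CMD. Smokers' hazards are multiplied by the ratios (HR) shown. Each arm is a mixture with 25% (control) or 20% (intervention) smokers, and that gap is held for life. Differences are intervention minus control per 1,000 people.

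| Smokers' CMD HR / death HR | CMD, 20 y | Deaths, 20 y | CMD, lifetime | Deaths, lifetime | Life-years |
|---|---|---|---|---|---|
| 1.4 / 2.0 | -2.8 | -9.9 | +2.7 | 0.0 | +310 |
| 1.8 / 2.0 | -6.3 | -10.6 | -0.8 | 0.0 | +328 |
| 1.4 / 1.5 | -3.5 | -5.6 | -0.4 | 0.0 | +196 |
| 2.0 / 1.5 | -8.9 | -6.5 | -5.3 | 0.0 | +224 |
| 1.4 / 2.0, CMD incidence also 1% lower in the intervention arm | -5.2 | -10.2 | -0.1 | 0.0 | +326 |
| 1.4 / 2.0, CMD incidence also 2% lower in the intervention arm | -7.6 | -10.5 | -3.0 | 0.0 | +341 |

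**4. A second model with other assumed rates.** From age 57 to 117: CMD incidence 0.02 × exp(0.04t), other-cause mortality 0.004 × exp(0.1t), excess mortality after CMD 0.01 × exp(0.07t). The control arm has 620.8 lifetime CMD cases and 1,000.0 deaths per 1,000, and 24.747 life-years per person.

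| Multipliers in the intervention arm | Lifetime CMD (change) | Lifetime deaths | Life-years per person (change per 1,000) |
|---|---|---|---|
| incidence × 0.90 | 588.5 (-32.3) | 1,000.0 | 24.962 (+215) |
| incidence × 0.90, mortality × 0.90 | 606.7 (-14.1) | 1,000.0 | 25.576 (+829) |
| incidence × 0.85, mortality × 0.95 | 579.7 (-41.1) | 1,000.0 | 25.382 (+635) |
| incidence × 0.95, mortality × 0.85 | 633.0 (+12.2) | 1,000.0 | 25.777 (+1,030) |
| mortality × 0.90 only | 638.9 (+18.1) | 1,000.0 | 25.342 (+595) |

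Lifetime CMD falls in three scenarios and rises in two. CMD-specific deaths, taken as those due to the excess hazard, are 329.3 in control. In the order of the table they are 311.1, 334.2, 312.2, 356.9 and 353.0, so they too move both ways.

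**5. Fixed horizons.** Here deaths do differ: in the second scenario 25.7, 73.5 and 278.9 at 5, 10 and 20 years, against 28.6, 81.2 and 303.5 in control. CMD at 20 years falls wherever incidence is lowered. It rises slightly (422.5 against 418.9) only where mortality alone changes and no CMD is prevented.

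**The case against.** The strongest reply is that the zero for deaths brings in a definition. The article does not say that mortality means a count of all-cause deaths, and the stated goal of reducing cardiometabolic mortality makes a CMD-specific reading natural. That count is not fixed at 100%. The model is called dynamic and population-based, and its cohort set-up is in sources that are not at hand. This stands, and the point is conditional for that reason. It does not rescue the endpoint: CMD-specific deaths over a lifetime share the ambiguity of the CMD count.

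Second, a reader might infer that the lifetime part cannot show benefit at all. The documents do not support that. Lifetime CMD fell in most of the cases above, and the single rise in the smoking illustration (+2.7) disappears if the other risk factors in endpoint 2 cut CMD incidence by 1%. The documents give none of the hazard ratios that would settle the sign.

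Third, the only operational sentence for endpoint 3 leaves out lifetime and mortality, so such results may never be produced, and QALYs are already planned under endpoint 4. Both are true. They limit the harm, but Table 2 and the heading still name the lifetime counts as primary.

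**Conclusion.** The point holds in a limited form. A lifetime count of all-cause deaths in a closed cohort carries no information about PPA CMR; this is exact and needs no assumed rates. The lifetime CMD count is ambiguous in direction: +2.7 to -5.3 per 1,000 in the smoking illustration, alongside about 200 to 340 life-years gained per 1,000, and +18.1 to -41.1 in the second model. Those sizes rest on assumed hazards and on effects that persist for life, and they are not forecasts of what the RIVM-CDM will give. The counts at 5, 10 and 20 years do not have the forced zero and remain usable.

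The consequence is for interpretation of the long-term projection. Endpoint 3 has no stated test, sample size or decision rule; the sample size rests on smoking. Nothing here suggests that the trial's one-year comparisons are affected.

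**What to change.** - In Table 2 and item 3, keep the CMD and mortality counts at 5, 10 and 20 years, and state whether mortality is all-cause or CMD-specific.
- At the lifetime horizon, replace the counts with life-years and/or QALYs gained from the RIVM-CDM, adding CMD-free life-years if wanted.
- Rewrite the method sentence under item 3 so that its outcomes and horizons match the endpoint.

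The cost is a change to Table 2 and item 3, plus some extra model reporting. QALYs are already planned, and the article says of the RIVM-CDM that "The model also contains data on costs of cardiovascular events and associated losses in quality of life". Whether it gives life-years and CMD-free life-years directly cannot be seen from the article and should be confirmed with the modelling team. The change does not remove the dependence on how long the one-year effect lasts, which the article acknowledges under Modeling.
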